### Trial interventions

#### Intervention in the experimental group

The proposed intervention was designed from literature reviews [6,39,40] and recent experimentations [31,33]. It integrates multiple methods to increase learning [46] and uses teaching tools adapted to normal aging changes [47]. The intervention consists of 2-hour meetings, once monthly, over three months. The duration of the intervention follows from the need for an incremental process that enables older adults to articulate preferences at their own pace and gradually integrate information on the benefits and limitations of ADs [28]. Furthermore, we expect repeated encounters to foster trusting relationships between dyad members and research personnel that are conducive to discussions on issues as sensitive as end-of-life care. The first and third meetings take place in the home of the older adult or proxy, a strategy likely to counter attrition [31]. The second meeting is an information session on ADs for groups of dyads.

Home meetings are led by trained social workers with extensive experience working with elders. The first visit begins with two thought-provoking vignettes that highlight the importance of communicating one's wishes about future medical care and research participation. The use of vignettes illustrating real-life experience has been shown to increase learning in elderly populations [47]. After eliciting reactions to the vignettes and exploring related issues, the facilitator summarizes the dyad-specific results of the concordance assessment and invites dyad members to discuss the reasons underlying their choices. Discussions seek to help older adults describe what makes their life worth living in specific, functional terms [48] and articulate their wishes, personal values and beliefs, so as to guide proxies in making decisions for them. Throughout the intervention, the social worker catalyzes discussion so that a shared understanding gradually develops between the older adult and his/her proxy.

The AD information session focuses on a guide entitled *My Preferences *that we designed for expressing wishes regarding future health care and research involvement. *My Preferences *also invites the signer to designate substitute decision-makers should he/she become incompetent. It was adapted from an AD form developed by Molloy and collaborators [49] for the *Let Me **Decide *(LMD) project. The LMD form has been successfully implemented in nursing homes and the community [50-53]. *My Preferences *was also inspired by documents developed by others for the same purpose [44,54,55]. Adaptation involved describing Quebec's legislation regarding substitute decision-making and adding a section for expressing desire to engage or not in studies of varying levels of risk and benefit.

*My Preferences *contains information on the purposes and uses of ADs. It addresses their practical limitations, including the impossibility of anticipating all future medical events [56-58]. The importance of reviewing ADs periodically is underscored given that preferences may change with the occurrence of significant life events, as predicted by the response shift theory [22,59,60]. More importantly, *My Preferences *emphasizes the difference between healthcare and research ADs so that subjects understand that research aims primarily at advancing knowledge for the benefit of future patients.

*My Preferences *was designed to be attractive to and effective with older adults [46,47,61]. It requires no more than 30 minutes to read and includes features such as:

■ paper with a matte surface,

■ contrasted background and text,

■ font size no smaller than 13 points,

■ short sentences using words as simple as possible,

■ glossary with medical and technical term definitions,

■ main idea of each paragraph highlighted in a box,

■ many illustrations,

■ space to write down instructions.

Before its use in the study, *My Preferences *was presented to 10 persons and subsequently revised for clarity.

The learning environment for the information session is also adapted for the elderly: a large, well-lit room allowing participants to move around easily, small group setting with chairs in a U shape layout to encourage interaction and discussion [47,62,63]. Various effective teaching tools are used throughout the information session [47,48,62-65], including:

■ a quiz to introduce and help assimilate new information,

■ a PowerPoint presentation in bright colors with large text,

■ videos showing people sharing their experiences (e.g., a person expressing difficulties due to not knowing the wishes of a loved one, a physician explaining the importance of advance planning for health care) or explaining how to use *My Preferences *to convey their wishes to family members,

■ activities encouraging participants to express their own point of view and to start completing *My Preferences *which then serves as an external memory aid to help overcome deficits in memory processes that are frequent among older adults.

At the third and final meeting, the social worker checks subjects' understanding of the information delivered at the group session, explains any terms in *My Preferences *that are still unfamiliar to the participants, and assists older adults in filling one out if desired. Those who elect to complete *My Preferences *at this stage are advised to inform family members and designated substitute decision-makers of its location and content. The social worker then requests a copy for analysis purposes. Content analyses of completed guides will allow us to determine whether the older adult designated a substitute decision-maker and/or expressed preferences regarding health care and research participation. Lastly, the social worker explores participants' satisfaction with the process and collects any suggestions they might have on how to improve the intervention.

#### Intervention in the control group

Approximately once monthly over three months, dyads assigned to the control group are invited to attend a 2-hour health education workshop on healthy lifestyle and preventive practices. The three workshops are adapted from a health education program aimed at improving self-care skills that has been effective with elderly people [66]. The number of meetings between dyads and the research team is identical across groups. However, experimental dyads meet individually and in subgroups whereas controls always convene in subgroups. Health education workshops are given by experienced nurses and allow for interaction within and between dyads. Once the study is complete, the AD information session given to experimental dyads will be offered to controls.

### Primary and secondary outcome measures

Prediction accuracy of substitute decision-making is the primary outcome and rate of completed guides, the secondary outcome. Concordance is the most important outcome of advance planning activities. However, we consider important to also measure the rate of documented preferences as these could raise less controversy in the event of incompetence than oral instructions given only to a single family member.

Concordance assessments are repeated at the end of the intervention (first posttest) and 6 months later (second posttest), according to the same procedure as at baseline. However, the first posttest uses new sets of treatments, sudden health events and research protocols to counter recall bias. Older adults' decisions under these various scenarios, and their proxies' predictions concerning those decisions, are recorded by the same research nurses who interviewed them at baseline. The second posttest will allow us to determine whether the positive effect of the intervention on prediction accuracy, if any, is maintained for at least six months. Copies of completed *My Preferences *are made at the first posttest and, for those who have yet to complete one, at the second posttest. Allocating six months to fill out *My Preferences *gives participants extra time to decide whether they want to commit directives in writing. A longer interval carries the risk of losing too many participants and no longer permits attributing the observed effect to the intervention, as opposed to more recent events that might have occurred in the meantime. Evidence regarding the impact of the intervention on the rate of completed guides will be based on written documents rather than self-report as the latter was found to overestimate true completion rates [39].

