**Methods/Design:**

Dyads (*n *= 240) comprising an older adult and his/her self-selected proxy are randomly allocated to the experimental or control group, after stratification for type of designated proxy and self-report of prior documentation of healthcare preferences. At baseline, clinical and research vignettes are used to elicit older adult preferences and assess the ability of their proxy to predict those preferences. Responses are elicited under four health states, ranging from the subject's current health state to severe dementia. For each state, we estimated the public costs of the healthcare services that would typically be provided to a patient under these scenarios. Experimental dyads are visited at home, twice, by a specially trained facilitator who communicates the dyad-specific results of the concordance assessment, helps older adults convey their wishes to their proxies, and offers assistance in completing a guide entitled *My Preferences *that we designed specifically for that purpose. In between these meetings, experimental dyads attend a group information session about *My Preferences*. Control dyads attend three monthly workshops aimed at promoting healthy behaviors. Concordance assessments are repeated at the end of the intervention and 6 months later to assess improvement in predictive accuracy and cost savings, if any. Copies of completed guides are made at the time of these assessments.

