Pearlman and collaborators [10] randomized 184 decisionally-competent veteran outpatients who did not have ADs in their hospital record. Experimental subjects were mailed a 52-page advance planning workbook and attended a 30-minute counseling session led by social workers immediately prior to their scheduled appointment with their healthcare providers. Control subjects were mailed the hospital's 8-page AD booklet 5 weeks prior to their office visit. Both books contained blank AD forms to complete. Four months after the index visit, ADs were filed in the medical chart twice as often for the intervention group (48% *vs*. 23%, *p *< 0.001). In addition, healthcare providers were more accurate in predicting the experimental subjects' treatment preferences, values and personal beliefs than for controls (*p *< 0.01 for all three comparisons). Patient-proxy concordance scores did not differ between intervention and control groups for preferences and values, but were higher in the intervention group for personal beliefs (67% *vs*. 56%, *p *= 0.04). Two features of the intervention may explain the better performance of healthcare providers over proxies. Providers were prompted to discuss planning with experimental subjects and had full access to their medical records, including any directives therein. By contrast, no component of the intervention promoted patient-proxy discussion which was entirely left to the patients' discretion. As stated by the authors: "this suggests that specific efforts should be made to include proxies in advance planning discussions with the patients".

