### The research objectives

The purpose of this trial is to assess the efficacy of a multimodal professionally-led advance planning intervention in 1) improving the accuracy of substitute decision-making (primary outcome) and 2) increasing the frequency of written ADs for health care and research (secondary outcome). Given current knowledge, the tested intervention includes an educational component on ADs and stimulates discussion between an older adult and his/her self-selected proxy with respect to end-of-life care and research participation. The study incorporates a cost analysis to measure public savings that result from improving proxy predictions of preferences.

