### Statistical analyses

Persons who decline participation or drop out will be compared to trial participants with parametric or non-parametric two-sample tests (depending on the distribution of the data) and results used to judge the scope of study findings. The same tests will be used to compare participants' baseline characteristics across study groups. Potential confounders and compliance indices will be candidates for adjustment when testing the impact of the intervention on the outcome measures [82]. All analyses will be based on allocation to the intervention or control group (i.e. by intention-to-treat). To account for losses to follow-up, analyses will be conducted in duplicate, first restricting the sample to the dyads for which we have complete follow-up data, then using a conservative approach by which dyads that do not provide such data are assumed not to have documented preferences and their baseline concordance levels are used for imputation [83].

The primary analysis will involve calculating composite scores of agreement across health states for each dyad. Calculations will generate a total concordance score as well as sub-scores derived from restricting summations to the clinical or research vignettes. Growth-curve modeling implemented with SAS PROC MIXED will be used to compare composite scores across time points and groups, an approach that accounts for the within-dyad correlation over time and accommodates missing values [84,85]. To further elucidate the impact of the intervention, secondary analyses will involve applying the same statistical procedure to the concordance sub-scores. A multivariable logistic model will be used to compare group-specific completion rates of *My Preferences *6 months post-intervention. The financial impact of the intervention will be investigated with Student's *t *test for independent samples or its non-parametric equivalent.

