**Figure 1 F1:**
[figure not shown]
**Study subjects flow chart (with estimated sample sizes in parentheses)**.

The above calculations assume that we will compare groups on posttest mean concordance scores as this allowed us to use the best available estimate of the likely effect of the intervention. However, our design involves repeated measurements of concordance over time that will be analyzed by growth-curve modeling, a more sophisticated approach that effectively uses all the available time points to estimate individual trajectories. Determination of suitable sample sizes for multilevel analyses is complex, in part because explicit formulas have not yet been derived for general models. However, simulations by Mass & Hox [86] show that between 50 and 100 units per group are needed to justify claims as to the absence of bias in standard error estimates. As shown in Figure 1, projected sample sizes are 120 units per group at baseline, 108 at posttest 1 and 86 at study completion. Since all data will contribute to some extent in estimating the model parameters, our approach to sample size estimation is conservative and protects against an underpowered study.

Lastly, as shown in Table 1, 86 dyads per group also provide sufficient power to detect a meaningful difference between groups for the secondary outcome.

**Table 1 T1:** Power to detect the intervention effect on documented preferences, according to three sources of information (*n *= 86 dyads per group, two-sided α = 0.05)

Source	Odds ratio (95% CI)	Event rate in the Control group	Event rate in the Experimental group	Power
Bravo *et al*. [39]	4.0 (1.6 - 10.4)	0.12*		95%
Patel *et al*. [87]	3.7 (1.5 - 9.4)	0.12*		92%
Pearlman *et al*. [10]		0.23	0.48	93%

* Derived from 13 RCTs included in our systematic review (mean = 0.12, sd = 0.182, range: 0 to 0.56) and applied to Patel *et al*. who did not report the mean event rate across control groups.

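### The aim is more written advance directives, but the outcome collected and modelled is completion of the study's own guide, which tends to favour the experimental arm

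*Protocol article*

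**What the plan says.** **Aim.** The research objectives section gives the second aim as "increasing the frequency of written ADs for health care and research (secondary outcome". The abstract speaks of documented preferences, and Table 1 is titled in the same terms.

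**Outcome and model.** The outcome section states: "Prediction accuracy of substitute decision-making is the primary outcome and rate of completed guides, the secondary outcome". It provides for copies of completed My Preferences at both posttests and requires documents, not self-report. The statistical analyses section says: "A multivariable logistic model will be used to compare group-specific completion rates of" My Preferences at 6 months. The section on compliance and losses asks withdrawn participants who refuse follow-up whether they have put their preferences in writing, but the copy then requested is of My Preferences.

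**Who is given the guide.** The abstract says that the experimental facilitator "offers assistance in completing a guide entitled" My Preferences. The intervention section describes it as designed by the team, presented at the experimental group session, started there, and completed with a social worker's help at the third meeting, where a copy is requested. Controls attend lifestyle workshops, and: "Once the study is complete, the AD information session given to experimental dyads will be offered to controls". The limitations section regards contamination as very unlikely.

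**Power.** The sample size section says that "86 dyads per group also provide sufficient power to detect a meaningful difference between groups for the secondary outcome". Table 1 uses control rates of 0.12 (two rows) and 0.23 (one row). The 0.23 comes from a trial of veteran outpatients that counted ADs filed in the chart. The background section says of the materials sent to its two arms: "Both books contained blank AD forms to complete".

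**The concern.** The aim and the power table concern one quantity, and the data collection and the model concern another. Completing My Preferences is one way of writing a directive, and the plan promotes that way in one arm only.

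An experimental participant who transfers existing wishes to the guide counts as an event. A control who writes the same wishes on another form does not. Randomisation is stratified on prior documentation, so the plan itself expects some participants to hold such documents.

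Three things are at stake:

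- the between-arm difference may be read as an effect on written ADs when part of it is a difference in which form was used;
- the control rates behind Table 1 do not describe the outcome to be analysed;
- with a control rate near zero the odds ratio becomes unstable, and with an empty control cell it is infinite.

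**Working it through.** **Inputs from Table 1.** n = 86 per arm and two-sided alpha 0.05. Row 1: control rate 0.12, odds ratio 4.0. Row 2: 0.12 and 3.7. Row 3: 0.23 against 0.48.

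**Step 1: reproduce Table 1.** The experimental rate is p2 = p1·OR / (1 − p1 + p1·OR).

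- Row 1: 0.48 / 1.36 = 0.353.
- Row 2: 0.444 / 1.324 = 0.335.

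The pooled-variance power is Φ{[(p2 − p1) − 1.96·√(2p̄(1 − p̄)/n)] / √([p1(1 − p1) + p2(1 − p2)]/n)}, where p̄ is the mean of p1 and p2. For row 1 this is (0.233 − 0.127) / 0.0623 = 1.70, and Φ(1.70) = 95.5%.

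| Row | Rates | Stated power | Recomputed |
|---|---|---|---|
| 1 | 0.12, 0.353 | 95% | 95.5% |
| 2 | 0.12, 0.335 | 92% | 92.7% |
| 3 | 0.23, 0.48 | 93% | 93.6% |

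The arithmetic is sound.

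**Step 2: what guide-only counting does to the difference.** Let pc and pe be the rates of any written AD in the control and experimental arms. Let g be the control rate of guide completion, and u the experimental rate of holding a directive on another form only. Then:

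- any-AD difference = pe − pc
- guide-only difference = (pe − u) − g
- excess = pc − g − u

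The excess is the control rate of other-form-only directives minus the same rate in the experimental arm. The documents give neither g nor u. The table assumes g = 0 and lets u vary, with the other-form background in the experimental arm no higher than pc.

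| Assumption about the experimental arm | Row 1 guide rate | Row 1 excess over 0.233 | Row 3 guide rate | Row 3 excess over 0.25 |
|---|---|---|---|---|
| Same background as controls, no overlap with the guide (u = pc) | 0.353 − 0.12 = 0.233 | 0 | 0.48 − 0.23 = 0.25 | 0 |
| Same background, independent of guide completion | 1 − 0.647/0.88 = 0.265 | 0.032 | 1 − 0.52/0.77 = 0.325 | 0.075 |
| Every directive is on the guide (u = 0) | 0.353 | 0.12 | 0.48 | 0.23 |

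If some controls do obtain the guide, the excess shrinks. At g = 0.05 and u = 0 the row 1 difference is 0.303, an excess of 0.07.

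**Step 3: the worst case for the test.** Suppose the arms do not differ in written ADs (both 0.12), but every experimental directive is on the guide. The guide-only test is then significant with probability 92% (g = 0), 73% (g = 0.02) or 38% (g = 0.05) by the normal approximation, and 95%, 67% or 29% by Fisher's exact test. This needs full substitution of the guide for other forms. With no substitution, no difference in written ADs would mean no difference in guide completion either.

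**Step 4: the model.** Separation needs an empty control cell. That is certain at g = 0 and has probability 0.98^86 = 18% at g = 0.02.

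**The case against.** No sentence says that controls are denied the guide. What is deferred until the study is complete is the information session. The text on collecting copies at the posttests is not limited to one arm, and the limitations section speaks of participants in general when it discusses the decision to complete the guide. A condensed article may omit such details. The wording may also be loose: the outcome section gives its rationale as documented preferences, and the imputation rule uses the same idea. Finally, the background names lack of access to forms as a barrier, so supplying one is a legitimate part of the intervention, and the limitations section calls AD promotion scarce in Quebec, so few controls may write anything new.

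Much of this stands, and it rules out four stronger readings that a reader might infer:

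- **The control rate is zero by design.** This is a strong inference from where the guide appears, but it is not stated.
- **The effect is overstated by half** (35 points against 23). That is the top of the range. It assumes no control uses the guide and no experimental participant holds a directive on another form only.
- **Table 1 is wrong.** Its powers reproduce. Nor is power lost by counting guides: at g = 0, even 23% against 0% gives 99.8%. A reader might also take both control rates as rates of any written AD, but the 0.23 is for ADs filed in charts, and the definitions behind the 0.12 are not shown.
- **The logistic model must fail.** It does so only if the control cell is empty.

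The objection does not remove the mismatch. Wherever a copy or a modelled rate is specified, only My Preferences is named, and no other document is collected. If controls seldom write directives, 0.12 and 0.23 are poor planning rates. If they do write them, the outcome misses them.

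**Conclusion.** The point holds as a conflict between the stated aim and the analysed outcome. Followed as written, the comparison tends to overstate the effect on written ADs. On Table 1's row 1 rates with g = 0, the excess is 0 to 12 points on a true difference of 23, and about 3 points if other-form directives and guide completion are independent. On the row 3 rates it is 0 to 23 points on 25. The size cannot be pinned down, because the plan collects neither the control guide rate nor directives on other forms.

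A claim limited to uptake of the guide would not be biased, but it would not answer the second objective. The primary outcome, its sample size and the cost analysis are untouched. This should be fixed, but it does not threaten the trial's main question.

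**What to change.** Define the secondary outcome as any written document of health-care or research preferences, on any form, completed or updated after randomisation and verified by a copy. Request it with identical wording in both arms at both posttests and in the contact with drop-outs. Compare the arms on that outcome, adjusting for the prior-documentation stratum. Report My Preferences completion descriptively, as uptake in the experimental arm. State whether controls can obtain the guide before the second posttest.

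Table 1 then refers to the outcome that is analysed and its powers can stay. The cost is one changed question at each contact and some analysis wording, and the apparent effect may be smaller. The question must be in place before the posttests, since documents not requested then may not be recoverable later.
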